# Treatment of unilateral spatial neglect after stroke using transcranial direct current stimulation (ELETRON trial): study protocol for a randomized controlled trial

**DOI:** 10.1186/s13063-016-1598-4

**Published:** 2016-10-03

**Keywords:** Stroke, Unilateral spatial neglect, Transcranial direct current stimulation

## Abstract

**Background:**

Unilateral spatial neglect (USN) is characterized by the inability to report or respond to people or objects that are presented in the spatial hemisphere that is contralateral to the lesioned hemisphere of the brain. USN has been associated with poor functional outcomes and long stays in hospitals and rehabilitation centers. Noninvasive brain stimulation, such as transcranial direct current stimulation (tDCS), has been used in people who have been affected by USN after stroke. The effects of such treatment could provide new insights for health professionals and policy-makers. The aim of this study will be to evaluate the effectiveness and safety of tDCS for USN after stroke.

**Methods:**

A prospective randomized controlled trial with two parallel groups will be conducted, which will aim to recruit 60 patients with USN after ischemic or hemorrhagic stroke. Participants will be randomly placed into the following four treatment groups: (1) anodal tDCS over the right parietal lobe (*n* = 15), (2) cathodal tDCS over the left parietal lobe (*n* = 15), (3) a sham group of anodal tDCS over the right parietal lobe (*n* = 15), and (4) a sham group of cathodal tDCS over the left parietal lobe (*n* = 15). Blinded assessors will conduct two baseline assessments and one post-intervention assessment. The primary outcome measure will be the level of USN as assessed by the conventional Behavioral Inattention Tasks and the Catherine Bergego Scale. Secondary measures will include neurological capacity (based on the Scandinavian Stroke Scale), functional capacity (based on the Functional Independence Measure and Modified Rankin Scale), autonomy (based on the Barthel Index), and quality of life (based on the EuroQol-5D). Group allocation will be concealed, and all analyses will be based on an intention-to-treat principle.

**Discussion:**

This study will explore the effects of more than 15 sessions of tDCS on the level of USN, functional capacity, autonomy, and quality of life in patients with USN after stroke. This proposed study has the potential to identify a new, evidence-based intervention that can enhance perception and independent living in patients with USN after stroke.

**Trial registration:**

REBEC - RBR-78jvzx, registered on 13 March 2016.

## Background

Unilateral spatial neglect (USN) clinically manifests when an individual does not respond to any tactile or visual stimulus on one side of the body or hemispherical space. Such unresponsiveness cannot be attributed to a sensory deficit or a primary motor deficit. This condition makes it difficult for a patient to report, respond to, guide, or interpret any stimulus that is received from the affected side [1–3]. Often a USN is associated with lesions in the right hemisphere of the brain, particularly in the parietal lobe [4–7], or the right posterior parietal lobe [8, 9]. USN is associated with a poor prognosis and the need for long periods of hospitalization [10–14].

Currently, the procedures that are used to evaluate USN are composed of tasks that use pen and paper to distinguish cancellation targets or simultaneous touch [15, 16]. Four tests have been proposed to assess USN, namely, the Face-Hand Test (FHT), which is used to promote simultaneous dual sensory stimulation in individuals [17–19]; the Line Cancellation Task [20, 21] or Star Cancellation [22], both of which are used to grade the severity of the USN based on the number of lines or stars cancelled; and the Line Bisection Task [23, 24] which is used to observe deviation from the midline of a space. The cancellation and bisection tests are used consistently in the clinic and exhibit high sensitivity and specificity for detecting USN [25, 26]. In addition to the cancellation and bisection tests, Azouvi et al. (2003) developed a specific scale based on 10 activities of daily living that can be changed by USN. This scale is typically used during the chronic period after a stroke to measure the efficacy of the treatments for symptom regression [27].

Since the early 1970s, various rehabilitation techniques have been proposed to reduce the disability that is caused by USN after stroke. Among them include techniques for noninvasive neuromodulation through brain stimulation, such as, transcranial magnetic stimulation (rTMS) and transcranial direct current stimulation (tDCS), which create low-intensity electrical currents in the brain to change the excitability of cortical regions [28, 29]. Recent studies suggest that noninvasive brain stimulation techniques can aid in the rehabilitation of patients with stroke to promote the recovery of function [30–33].

tDCS reversibly polarizes regions of the brain via the topical application of low-intensity direct currents to change the potential and modulation of transneuronal membrane excitability levels and firing rates [31, 34]. The tDCS-induced polarization effect in the brain varies depending on electrode polarity, wherein the anodal stimulation (positive electrode) increases cortical excitability, while the cathodal stimulation (negative electrode) decreases excitability [35]. Recent human studies have shown that anodal polarization increases the excitability of the motor, visual, and prefrontal cortices, with an improved performance of motor skills [36], working memory [37], and verbal fluency [38].

Few studies have been designed to evaluate the effect of tDCS on the USN syndrome after stroke. A randomized controlled trial conducted by Ko et al. (2008) in 15 patients with USN after stroke observed improvements in the performance of the Line Cancellation Task, Figure and Shape Copying, and the Line Bisection Task after anodal polarization using tDCS of the right posterior parietal region [39]. Using tDCS in 10 patients with USN after stroke, Sparing et al. (2009) observed that inhibitory cathodal stimulation applied to the uninjured posterior parietal cortex, and excitatory anodal stimulation of the lesioned posterior parietal cortex, reduced the degree of USN [40].

In a clinical trial conducted in 10 patients with USN after stroke in the chronic phase, Sunwoo et al. (2013) evaluated the following three types of stimulation: (1) simultaneous anodal stimulation to the right parietal cortex and cathodal stimulation to the left parietal cortex, (2) single-mode anodal stimulation to the right parietal cortex, and (3) sham stimulation to control for the placebo effect. The authors observed an improvement in the performance of the Line Bisection Tasks for the simultaneous and single-mode stimulation types. Moreover, the effect for simultaneous stimulation was greater than that compared to the other two stimulation types [41]. A recent study evaluated the application of tDCS in five sessions, each of 20 min, in five individuals with USN in the chronic phase of stroke. Cathodal stimulation was applied to the P3 region (left parietal cortex) and anodal stimulation was applied to the P4 region (right parietal cortex) according to the international electroencephalogram system. The results were not statistically significant and the degree of USN was not reduced at the end of treatment. These results suggest that randomized controlled trials should include the highest possible number of patients [42].

USN after stroke can be caused by a hemispherical imbalance of cerebral electrical activity with the injured area showing no decrease in cortical excitability. Recent studies suggest that spatial perception could be improved by restoring the balance of hemispherical activity through tDCS [40–43]. In addition, USN has been associated with a worse functional outcome, a longer retention of patients in rehabilitation centers, a high risk of falls, and the need for a wheelchair. Such outcomes decrease productivity and quality of life compared to other patients without USN after stroke [13, 14, 43].

Several studies have reported that tDCS can improve performance in tasks that assess spatial orientation after USN such as Line Bisection and Line Cancellation Tasks. However, these studies do not report a complementary reduction in long-term disability or an improvement in patient quality of life. Because tDCS is a cost-effective noninvasive procedure for brain stimulation compared to, for example, magnetic stimulation, we propose the present research to try to establish whether it could in fact lead to the aforementioned quality of life improvements.

### Aims

The principal objective of this study in patients with USN after stroke is to evaluate the efficacy and safety of 15 sessions of tDCS versus placebo in ameliorating USN. We hypothesize that tDCS will induce changes in the neuronal activity of the posterior parietal lobe that will reduce USN presentation in patients after stroke.

In addition, we will assess the effects of tDCS on the capacity of function, level of paralysis, and quality of life.

## Methods

### Design

This single-center, randomized, placebo-controlled, double-blind, parallel-group study of 60 patients with USN will be conducted in accordance with the Consolidated Standards of Reporting Trials (CONSORT) 2010 flow diagram [44] (Figs. 1 and 2).

**Fig. 1 Fig1:**
[figure not shown]
Study flow diagram for anodal transcranial direct current stimulation (tDCS) stimulation

**Fig. 2 Fig2:**
[figure not shown]
Study flow diagram for cathodal transcranial direct current stimulation (tDCS) stimulation

### Sample size

We estimate a minimum sample size per group of 15 assuming: simple random sampling; type I and II error probabilities equal 0.05 and 0.20, respectively; the absence of confounders; normal distribution for the outcome “percentage of deviation” with a mean baseline equal to a 15 % reduction in the outcome after tDCS; an estimated reduction of between 8 and 3 % for the sham group; and a variation coefficient of 20 %.

### Location and setting

All assessments will be conducted at the Botucatu Medical School within the Department of Neurology and Center of Rehabilitation, Botucatu, Brazil.

## Participants

### Inclusion criteria

Individuals of 18–85 years of age and of either sex, with USN after stroke diagnosis within 15 weeks of the start of stroke symptoms, will be included in this study. The patients will be recruited in the stroke unit by Botucatu Medical School, and will include patients with right-hand ischemic or hemorrhagic stroke in the right parietal lobe confirmed using computed tomography (CT) or magnetic resonance imaging (MRI). USN will be objectively diagnosed by conventional Behavior Inattention Tasks (BIT-C) with a cutoff of >129.

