### Procedures (template)

Individuals diagnosed with right-hand stroke after discharge from the hospital will be sent to the rehabilitation sector. All individuals with damage to the right hemisphere, as confirmed by a CT or MRI scan, will be invited to participate. The patient, a family member, or guardian must sign a Free and Informed Consent Form. After signing the Consent Form, the individuals will be evaluated to confirm their diagnosis using BIT-C, consisting of Star Cancellation (SC), Letter Cancellation (LC), Line Crossing (LiC), Line Bisection (LB), Figure and Shape Copying (FSC-A&B), and Representational Drawing (RD). After confirmation of the USN diagnosis (BIT-C >129), patients will be screened to clinical condition, the HAD, the Edinburgh Handedness Inventory to classify laterality, and checking of the excluded criteria for the tDCS application. After screening patients will be randomized into the following four groups: (1) treatment with anodal tDCS, (2) control with anodal tDCS (sham mode), (3) treatment with cathodal tDCS, (4) control with cathodal tDCS (sham mode). Individuals will be assessed using the Catherine Bergego Scale (CBS), the Mini-mental State Examination (MMSE), the National Institutes of Health Stroke Scale (NIHSS), the Functional Independence Measure (FIM), the Barthel Index, the Modified Rankin Scale (mRS), and the European Quality of Life Scale (EuroQol-5D) by an investigator who is blinded to the treatment that the patient received before the first session and after 1 week from the last tDCS session (Table 1).

**Table 1 Tab1:** Template of recommended content for the schedule of enrollment, interventions, and assessments

	Study period				
	Enrollment	Allocation	Post allocation		Close-out
Timepoint	−t_1_	0	t_1_	t_15_	t_16_
Enrollment:					
Eligibility screen	X				
Informed consent	X				
BIT-C and HAD^a^	X				
MMSE^b^	X				
EHI^c^	X				
Allocation		X			
Interventions:					
Anodal tDCS^d^			X	X	
Cathodal tDCS^e^			X	X	
Anodal placebo			X	X	
Cathodal placebo			X	X	
Assessments:					
BIT-C^a^					X
CBS^f^		X			X
NIHSS, FIM and BI^g^		X			X
mRS^h^		X			X
Quality of life^i^		X			X

^a^Conventional Behavior Inattention Tasks and Hospital Anxiety and Depression Scale

^b^Mini-mental State Examination

^c^Edinburgh Handedness Inventory

^d^Anodal tDCS applied over left parietal lobe (P3)

^e^Cathodal tDCS applied over right parietal lobe (P4)

^f^Catherine Bergego Scale

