### Primary outcome measures

Change in the degree of USN will be measured as follows: (1) D1, as the percentage of changed in range of BIT-C, and (2) D2, based on the CBS.

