### Secondary outcome measures

Disability, autonomy, and quality of life will be measured as follows: (1) D3, as the change in neurological status based on the NIHSS, (2) D4, as the change in functional independence based on the Barthel Index, (3) D5, as the change measured using the mRS, and (4) D6, as the change in quality of life based on the EuroQol-5D. For all of the outcomes (except for D6), the change after stimulation will be calculated as follows: 100 (*Vf* − *V0*)/*V0*, where *V0* is the value of the prerandomization variable and *Vf* is the variable value after 1 week of treatment.

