### Baseline assessments

#### USN evaluation

*Conventional Behavior Inattention Tasks (BIT-C)*: the six conventional tasks of the BIT-C will be administered, consisting of Star Cancellation (SC), Letter Cancellation (LC), Line Crossing (LiC), Line Bisection (LB), Figure and Shape Copying (FSC-A&B), and Representational Drawing (RD). The BIT-C is usually administered to diagnose USN and provides a range (0–146) and a cutoff score. For all USN tests, the examiner will place the test sheet in front of the patient with a distance of 60 cm between the paper and the glabella of the patient [47].

*Catherine Bergego Scale (CBS)*: this test will be used to measure the extent to which the USN interferes with daily tasks. The scale is divided into 10 activities each with a score of 0 to 3. The maximum scale score is 30 and the total indicates USN severity [27].

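### Neglect is confirmed at BIT-C above 129 on a 0–146 scale, which on the scale's apparent direction selects the unimpaired end and compresses primary outcome D1

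*Protocol article*

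**What the plan says.** Inclusion criteria in the protocol article gives the rule: "USN will be objectively diagnosed by conventional Behavior Inattention Tasks (BIT-C) with a cutoff of >129". Procedures (template) applies it as the step before screening: "After confirmation of the USN diagnosis (BIT-C >129), patients will be screened to clinical condition". The same inequality therefore appears in two sections, and both times it is what confirms neglect.

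USN evaluation gives the range but not the direction: "The BIT-C is usually administered to diagnose USN and provides a range (0–146) and a cutoff score". For the CBS, by contrast, the same section says that the total indicates severity. The nearest statement on direction is in Background, where the line and star cancellation tests are said to "grade the severity of the USN based on the number of lines or stars cancelled".

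BIT-C is also an outcome. Primary outcome measures defines "D1, as the percentage of changed in range of BIT-C", with the CBS as D2. The formula stands under Secondary outcome measures but is worded to cover D1: "For all of the outcomes (except for D6), the change after stimulation will be calculated as follows", namely 100(Vf − V0)/V0.

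**The concern.** Neglect is a failure to respond to stimuli on one side. On a task scored by targets cancelled, a patient with neglect cancels fewer and scores lower. If the BIT-C total follows its cancellation tasks, neglect lies at the low end, and a rule requiring more than 129 of 146 points selects the wrong side of the cutoff.

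BIT-C is the only objective test of neglect named for entry, so an inverted rule changes who is in the trial. Because D1 is the percentage change in the same score, the rule would also place every patient close to the ceiling of a primary outcome and leave little room for active and sham stimulation to differ.

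**Working it through.** **Inputs**
- Entry rule: BIT-C above 129 (Inclusion criteria; Procedures).
- Scale: 0 to 146 (USN evaluation), taken in whole points, so 147 possible scores.
- D1 = 100(Vf − V0)/V0 (Primary and Secondary outcome measures).
- Planned effect: 15 % reduction after tDCS in *percentage of deviation* (Sample size).
- Direction: higher means less neglect. This is inferred from Background and not stated.

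The plan gives no headroom figure for BIT-C, so there is none to reproduce. Its group size of 15 does not use the threshold and is a separate matter.

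**Step 1. Who is admitted.** Scores 130 to 146 number 146 − 130 + 1 = 17. As a share, 17/147 = 11.6 %, all at the top of the scale. Every score of 129 or below is excluded.

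**Step 2. Largest possible gain on D1**, with perfect recovery (Vf = 146), is 100(146 − V0)/V0:

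| Baseline V0 | Largest D1 gain |
|---|---|
| 130 | 16/130 = 12.3 % |
| 135 | 11/135 = 8.1 % |
| 140 | 6/140 = 4.3 % |
| 146 | 0/146 = 0 % |

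If baselines were spread evenly over 130 to 146 (an assumption), the mean of these ceilings would be 5.9 %. If D1 were instead read as a share of the 146-point range, the ceiling would be 16/146 = 11.0 %.

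**Step 3. Comparison with 15 %, only if that figure applies to D1.** A gain of 15 % needs V0 × 1.15 ≤ 146, so V0 ≤ 146/1.15 = 126.96, which means a baseline of 126 or less. No patient admitted by the literal rule has such a baseline.

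**Step 4. The opposite direction.** If a high BIT-C meant more neglect, a score of 130 would be 130/146 = 89 % of the maximum deficit. A 15 % fall from 130 would end at 130 × 0.85 = 110.5 and from 146 at 146 × 0.85 = 124.1. Both are on the scale, so the ceiling in Steps 2 and 3 would disappear. The rule would then admit only near-maximal deficit.

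**The case against.** Four points deserve weight.

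- **The direction is inferred.** Background describes stand-alone cancellation tests, not the BIT-C total. By name, two of the six listed tasks are cancellation tasks, or three if Line Crossing is counted, and no weights are given. This stands, and the finding is worded accordingly. The opposite reading removes the ceiling but would make near-total failure the definition of a one-sided disorder. The article gives no severity distribution, so that reading can be called implausible but not excluded.
- **The 15 % is not tied to BIT-C.** A reader might infer that the planned effect is impossible for every eligible patient. The document does not support that: Sample size speaks of a reduction in an undefined quantity, whereas improvement on BIT-C would be an increase. Only the conditional statement holds.
- **The CBS is also a primary outcome.** A reader might infer that the trial cannot answer its question at all. That is too strong, because a BIT-C threshold does not arithmetically cap the CBS. Even so, patients without neglect would be expected to start near 0 on the CBS, and the change formula is undefined at V0 = 0.
- **It may be a reversed symbol.** Both passages speak of diagnosing neglect, so the intent to enrol such patients is clear. Nothing shows that screening used the literal rule, and it should not be inferred that patients without neglect have been enrolled. The published rule still says the reverse of that apparent intent and needs correcting.

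**Conclusion.** The concern holds in a limited form. The entry rule, written the same way in two sections, conflicts with the apparent direction of the scale. Assuming that higher means less neglect and that scores are whole points, it admits 17 of 147 possible scores, excludes patients with neglect, and caps the D1 gain at 12.3 % at best and 0 % at worst. That compression does not depend on what effect was planned. The shortfall against 15 % depends on one further assumption, that *percentage of deviation* means D1. The text needs correcting before the trial relies on it: it either describes the wrong population or misdescribes the rule actually used.

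**What to change.** - In USN evaluation, state which end of BIT-C is impaired.
- In Inclusion criteria and Procedures (template), correct the inequality so that neglect lies on the impaired side of the cutoff. Verify the exact boundary, including whether 129 itself counts, against the instrument manual, since the article does not settle it.
- In Sample size, say whether *percentage of deviation* is D1. If it is, note that reversing the inequality does not remove the ceiling for everyone: the largest gain is 14.96 % at baseline 127, 14.1 % at 128 and 13.2 % at 129.
- Trial status is given as ongoing, so check the screening form and any patients already enrolled against the corrected rule.

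The cost is a few wording changes and an eligibility check. If screening already used the intended side of the cutoff, nothing else changes. If the literal rule was used, some patients may have to be reclassified, with consequences for the analysis population and possibly for recruitment.

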### Exclusion criteria

Excluded individuals will include any patients with metal-in-cranium injuries near the electrode placement area, a cardiac pacemaker in situ, intracerebral vascular clips or any other electrically sensitive support system, clinical instability, epilepsy, severe cognitive impairment, bilateral lesions, global aphasia, previous visual disturbances, depression with scores >8 in the Hospital Anxiety and Depression Scale (HAD), pregnancy, or other neurological diseases.

### Procedures (template)

Individuals diagnosed with right-hand stroke after discharge from the hospital will be sent to the rehabilitation sector. All individuals with damage to the right hemisphere, as confirmed by a CT or MRI scan, will be invited to participate. The patient, a family member, or guardian must sign a Free and Informed Consent Form. After signing the Consent Form, the individuals will be evaluated to confirm their diagnosis using BIT-C, consisting of Star Cancellation (SC), Letter Cancellation (LC), Line Crossing (LiC), Line Bisection (LB), Figure and Shape Copying (FSC-A&B), and Representational Drawing (RD). After confirmation of the USN diagnosis (BIT-C >129), patients will be screened to clinical condition, the HAD, the Edinburgh Handedness Inventory to classify laterality, and checking of the excluded criteria for the tDCS application. After screening patients will be randomized into the following four groups: (1) treatment with anodal tDCS, (2) control with anodal tDCS (sham mode), (3) treatment with cathodal tDCS, (4) control with cathodal tDCS (sham mode). Individuals will be assessed using the Catherine Bergego Scale (CBS), the Mini-mental State Examination (MMSE), the National Institutes of Health Stroke Scale (NIHSS), the Functional Independence Measure (FIM), the Barthel Index, the Modified Rankin Scale (mRS), and the European Quality of Life Scale (EuroQol-5D) by an investigator who is blinded to the treatment that the patient received before the first session and after 1 week from the last tDCS session (Table 1).

**Table 1 Tab1:** Template of recommended content for the schedule of enrollment, interventions, and assessments

	Study period				
	Enrollment	Allocation	Post allocation		Close-out
Timepoint	−t_1_	0	t_1_	t_15_	t_16_
Enrollment:					
Eligibility screen	X				
Informed consent	X				
BIT-C and HAD^a^	X				
MMSE^b^	X				
EHI^c^	X				
Allocation		X			
Interventions:					
Anodal tDCS^d^			X	X	
Cathodal tDCS^e^			X	X	
Anodal placebo			X	X	
Cathodal placebo			X	X	
Assessments:					
BIT-C^a^					X
CBS^f^		X			X
NIHSS, FIM and BI^g^		X			X
mRS^h^		X			X
Quality of life^i^		X			X

^a^Conventional Behavior Inattention Tasks and Hospital Anxiety and Depression Scale

^b^Mini-mental State Examination

^c^Edinburgh Handedness Inventory

^d^Anodal tDCS applied over left parietal lobe (P3)

^e^Cathodal tDCS applied over right parietal lobe (P4)

^f^Catherine Bergego Scale

^g^National Institutes of Health Stroke Scale, Functional Independence Measure and Barthel Index

^h^Modified Rankin Scale

^i^Quality of life measured by The European Quality of Life Scale (EuroQol 5D)

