### Intervention

The tDCS will be applied in accordance with the technique used by Sparing et al. [40]. The patient will be placed in a room with minimal external influences (noise, lamps, and electromagnetic waves), and positioned in a sitting posture with their arms and torso supported on a table at 45°. For stimulation of the right and left posterior parietal lobes, after shaving and cleansing the skin with alcohol, the electrodes will be placed in positions P4 and P3 of the 10/20 International System of Electroencephalography. The reference electrodes will be placed on the cranial vertex (Cz). Four groups of patients will receive stimulation as follows: group 1, right anodal stimulation (P4 anode, reference Cz), group 2, sham control for right anodal stimulation (P4 anode, reference Cz), group 3, left cathodal stimulation (P3 cathode, reference Cz), and group 4, sham control for left cathodal stimulation (P3 cathode, reference Cz). For stimulation, sponge surface electrodes (5 cm × 5 cm square) will be soaked in saline. A continuous current of 1 mA in intensity and a resistance of less than 10 kΩ will be applied for 1200 s with ramping up for 30 s and ramping down for 30 s according to international safety guidelines [38]. The tDCS will be applied using an electrical stimulator, namely the battery-powered DC-Stimulator Plus model, NeuroConn®.

A total of 15 sessions will be performed using a schedule of three times a week for 5 weeks, wherein a blinded examiner evaluates the patient before the beginning of the first session and 1 week after the last session. For the control group (sham), patients will be placed in the same room and position, but the current that will be applied to each control group will be shut off after 30 s.

The physiotherapy protocol will be delivered after tDCS and will be composed of saccadic eye movement training with visual scanning exercises (VSEs) integrated with task-specific activities. The VSEs integrated with task-specific activities will consist of dual-task activities, which require the ability to allocate information-processing resources between two tasks and to maintain sufficient attention on the visual scanning task during the dual-task performance. The guideline of the VSEs integrated with task specific activities and the principles of progression of these exercises follow van Wyk et al. [45], with session durations of approximately 45 min.

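### Table 1 footnotes d and e give both active arms the opposite side and electrode from the Abstract and the Intervention section

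*Protocol article*

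**What the plan says.** Three places in the protocol article assign a side to the active arms.

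- **Abstract, Methods.** The active arms are "anodal tDCS over the right parietal lobe" and "cathodal tDCS over the left parietal lobe", each with 15 patients. Each sham arm is given the site of its active counterpart.
- **Intervention.** The same assignment appears with electrode codes: "group 1, right anodal stimulation (P4 anode, reference Cz" and "group 3, left cathodal stimulation (P3 cathode, reference Cz". Groups 2 and 4 are the matching shams.
- **Procedures (template), Table 1.** Footnote d, on the active anodal row, reads "Anodal tDCS applied over left parietal lobe (P3". Footnote e, on the active cathodal row, reads "Cathodal tDCS applied over right parietal lobe (P4". The two placebo rows carry no footnote on site.

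Two other statements bear on what the difference means. The Background says that "the anodal stimulation (positive electrode) increases cortical excitability, while the cathodal stimulation (negative electrode) decreases excitability". The Inclusion criteria restrict entry to ischemic or hemorrhagic stroke of the right parietal lobe, and the Exclusion criteria remove bilateral lesions.

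**The concern.** Side and polarity define what each active arm is. The schedule table gives one definition, and the Abstract and Intervention section give the opposite one under the same arm names. All are current text of a single document.

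The meaning of the planned comparisons is at stake. The Data analysis section compares anodal with cathodal stimulation and active with sham, and the Discussion aims to identify the better of the two types. Neither result can be interpreted unless each arm name stands for one montage. If some sessions followed the footnotes and others the Intervention section, a single arm would contain two different interventions.

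**Working it through.** No figure is involved, so the check sets the texts side by side.

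| Place | Active anodal | Active cathodal | Sham site stated? |
|---|---|---|---|
| Abstract, Methods | right parietal | left parietal | yes, same as active counterpart |
| Intervention | right, P4, reference Cz | left, P3, reference Cz | yes, same as active counterpart |
| Table 1, footnotes d and e | left, P3 | right, P4 | no |

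1. **Is it a reading error from the PDF?** No. Each footnote is coherent in itself: left goes with P3 and right with P4, the same pairing that the Intervention section uses. A garbled side or code would have produced a mismatch within a footnote. No redaction or amendment log is involved.

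2. **Does nearby text settle it?** No. The list of four groups in the Procedures section names the arms by polarity and sham status only, so within that section the footnotes are the only statement of side. Group numbers do not help either: group 2 is active cathodal in the Abstract but sham anodal in the Procedures and Intervention sections.

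3. **Does the difference matter on the article's own terms?** Take the stated polarity effect (anode raises, cathode lowers) and the stated lesion side (right).
   - Abstract and Intervention: the anodal arm raises excitability on the lesioned side; the cathodal arm lowers it on the intact side.
   - Table 1 footnotes: the anodal arm raises excitability on the intact side; the cathodal arm lowers it on the lesioned side.

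   The intended effects on the two hemispheres are opposite.

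4. **How many patients does it concern?** The direct conflict covers the two active arms: 15 + 15 = 30 of 60 planned patients. The sham arms are outside it because Table 1 gives them no site.

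**The case against.** The strongest reply is that the Intervention section is the operative definition. It lists all four groups with side, electrode, polarity and reference, and the Abstract agrees with it. It also says that it follows the technique of a cited 10-patient study, which the Background describes as anodal on the lesioned side and cathodal on the uninjured side. Against that stand two footnotes to a table captioned as a template. They give no reference electrode, current, duration or sham procedure, so nobody could deliver a session from them alone. On this view they look like a left/right transposition in one place. The trial is single-center by its Design section, and the article condenses a fuller protocol that is not shown.

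Much of this stands, and it limits what can be claimed. It does not remove the contradiction, because no text says which statement prevails.

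A reader might infer four stronger things that the document does not support:

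- **Patients received a swapped montage, so the treatment effect is diluted.** Nothing shows that operators work from Table 1 or that any session followed the footnotes.
- **The clinical effect would reverse, or patients would be harmed.** Opposite intended effects on excitability follow from the text; opposite effects on neglect do not. The article reports no clinical results for left anodal or right cathodal stimulation in neglect, and it names no hazard from the footnote montage.
- **The footnotes contradict the trial's hypothesis.** Hemispheric balance appears in the Background as something that recent studies suggest. The hypothesis under Aims names neither side nor polarity.
- **The sham arms are affected too.** The footnotes attach only to the active rows.

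**Conclusion.** The text is wrong as written and has to be corrected. Footnotes d and e of Table 1 reverse the side and electrode of both active arms relative to the Abstract and the Intervention section, and nothing in the article reconciles them. The conflict concerns the definition of the intervention for 30 of 60 planned patients. That is the most that could be directly affected, not an estimate of how many were.

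The statement about opposite intended effects rests only on the article's own account of polarity and on right-sided lesions being the ones enrolled. Any damage to the comparisons depends on sessions having followed the footnotes, which is unknown. No size is put on it, because that would require assuming both the fraction of such sessions and their clinical effect. This conclusion takes no position on which montage is right.

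**What to change.** The sponsor should reconcile the Abstract, the Table 1 footnotes and the Intervention section so that each arm has one electrode site and one polarity, with the sham arms still matched to their active counterparts. The operator instructions should then be checked against the agreed text. Since the trial status is given as ongoing, the sponsor should also confirm, from whatever session records exist, which montage was delivered to patients already treated, and report any departure.

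The cost is small: a correction to two footnotes or to the text they conflict with, a comparison with the operator instructions, and a record check for the active-arm patients treated so far. Reconciling the text does not itself require a change to the sample size, the visit schedule or the analysis model.
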